### Assessments

Participants will complete questionnaires before starting the intervention (T0), 2 weeks after completing the intervention (T1), and 1 month after T1 (T2). Patients and their partners will also complete weekly diaries, starting 1 week before the intervention and ending 1 week after the intervention is completed. All questionnaires and diaries will be provided on the web through a secure, web-based application called REDCap (Research Electronic Data Capture) [35]. Patients and their partners will receive a link sent to their personal email and will be encouraged to respond independently from each other. In the event of nonresponse to the questionnaire, participants will receive a reminder email after 7 days and a second reminder after another 7 days of nonresponse. In case a diary assessment is missed, participants will receive a reminder the next day, and if 2 consecutive diaries have not been responded to, the assistant will call the participant to discuss possible problems. Therapists will also keep a therapist log to register data on intervention delivery, and the research assistant will keep a recruitment log to register data on recruitment and study adherence. A subsample of 5 patients with cancer and 5 partners (anticipated sample sizes), as well as all therapists providing the COMPANION intervention, will be invited to participate in separate focus groups. Patients and partners will be sampled purposefully (ie, based on high vs low levels of adherence or intervention satisfaction) and can be invited independently from each other.

### Sample Size Calculation

The study is powered to test the potential efficacy of the couple intervention in reducing patient fatigue (ie, the second primary research aim). Patients’ baseline (T0) and postintervention (T1) scores on the Checklist Individual Strength, subscale Fatigue Severity (CIS-fatigue) will be analyzed with a 1-tailed matched pairs *t* test. G*Power analysis indicated that 27 patients are required to detect a medium effect (0.5) with an α of .05 and a power of 0.8 (1-tailed). We expect CIS-fatigue scores at T1 to be significantly lower than CIS-fatigue scores at T0. We will conduct a 1-sided test given the gain in power as compared to a 2-sided test and evidence that an increase in mean fatigue is unlikely to occur [31]. Based on the drop-out rate in our previous trial [31] and a recent review of the attrition rate in couple-based interventions for cancer [36], we assume a 20% drop-out rate. Hence, we will aim to include a total of 34 couples.

### Intervention

COMPANION is a couple intervention developed from an evidence-based patient-centered eMBCT that aims to change the patient’s behavioral and cognitive reactions to cancer-related stressors, including fatigue [31]. Like the patient-centered eMBCT, COMPANION is web-based and guided remotely by a trained therapist. However, COMPANION also involves the patient’s partner in the treatment. The intervention consists of 9 sessions, which take approximately 15 to 20 weeks to complete (ie, the intervals between sessions are flexible to accommodate holidays and other commitments). Patients will have access to a secure web-based platform where they will receive written information about a specific theme for each session. Partners will have access to these materials through the patient. Table 1 provides an overview of all 9 sessions. Participants will be provided with audio files to practice different mindfulness-based cognitive-behavioral exercises each session. Patients will document their experiences in their personal log and perform exercises for approximately 30 minutes, 6 days a week. The exercises comprise topics such as relaxation, eating with awareness, moving with awareness, 3-minute breathing exercises, or meditation. Apart from the video call consultations, communication with the therapist will be mostly asynchronous, meaning that the therapist reads the experiences in the logs and provides feedback once a week. Adaptations compared to the patient-centered version were based on the findings from the preceding needs assessment among patients, partners, and therapists ([name] et al, unpublished data, 2023). These adaptations mainly concerned: 3 video call consultations between patient, partner, and therapist; psychoeducation for the partner; additional exercises for patient and partner (to be performed together or independently); and an extra session focused on the couple’s mutual relationship and mindful communication about fatigue. Together with their therapist, couples can decide how and to what extent their partner will be involved.

**Table 1 table1:** Modules of COMPANION.

Theme of module	Web-based psychoeducation	Exercises
Module 1: Fatigue and the automatic pilot	Automatic pilot Coping with fatigue Patients formulate treatment goals	Practice relaxation and awareness of the body with an audio file “bodyscan” Register experiences with the “bodyscan” Register experiences with eating with awareness
Module 2: Practice being open-minded	Coping with pain and fatigue Handling thoughts during breathing exercise Tips for better sleep quality	“Bodyscan” with muscle tension Breathing exercise Register experiences with these exercises Register awareness during a specific activity Register awareness during pleasant moments
Module 3: Dealing with boundaries	Awareness of handling physical and emotional boundaries Cultivating acceptance	Moving with awareness and a 3-minute breathing exercise, alternated with previous exercises Register experiences with these exercises Register awareness about what happens when meeting boundaries
Module 4: Dealing with stress	Patience Recognizing automatic negative cognitions Recognizing daily stress-inducing experiences and their emotional impact	Using the senses (hearing, seeing, and feeling) with awareness Alternating with previous exercises
Module 5: Communication	How to communicate about cancer-related fatigue How to communicate mindful of your own and others’ thoughts and feelings	Mindful communication exercise Alternating with previous exercises
Module 6: Dealing with feelings	Accept things as they are Coping with negative emotions through acceptance	Allowing intense feelings by focusing on present awareness of sensations in the body Alternating with previous exercises
Module 7: Dealing with thoughts and anxiety	Dealing with thoughts and fears Interaction between thoughts, emotions, and behaviors Physiology of fear	Becoming aware of automatic negative thinking Making a list of these thoughts Alternating with previous exercises
Module 8: Self-care	Self-care	Compose own practice schedule by choosing from previous exercises Making a list of helpful cognitions
Module 9: From stress and fatigue to strength	Patients continue practice with their own practice schedule	Writing about what helps their practice Formulation of potential pitfalls in the future and composition of self-management strategies

### Therapist Training and Treatment Integrity

Therapists at the HDI will deliver COMPANION. They all fulfill the criteria established by the United Kingdom Mindfulness-Based Teacher Therapist Network Good Practice Guidelines for teaching mindfulness-based interventions [37]. They will be trained in providing the couple intervention by an experienced therapist and a researcher from the COMPANION project team. This training starts with a preparatory self-study assignment using the web-based COMPANION treatment environment (a web portal for therapists). Next, therapists participate in an interactive training session addressing the content of the new therapy, the role of the therapist within this new therapy (including exercises and suggestions for involving the partner and giving therapeutic feedback [38]), and the design and procedures of the COMPANION pilot trial. All information is documented in a detailed written manual for therapists. Regular supervision will take place during the pilot trial, led by a member of the COMPANION project team who is a registered supervisor at the Dutch Society for Cognitive Behavioral Therapy. This supervisor has 15 years of experience in psycho-oncology, including 12 years of work experience with the patient-centered eMBCT for CCRF.

### Measures

Table 2 provides an overview of all the constructs to be assessed. For conciseness, we have only described the key measures. Where possible, we chose validated and widely used instruments in the field. Table 2 provides references for measures not described here.

**Table 2 table2:** Overview of instruments, questionnaires, and assessment time points. Unless otherwise indicated, both patients and their partners complete questionnaires, and they report on their own health, perception, and state. Partner version of scales are own adaptations.

Construct		Instrument or type of assessment	Assessment time points				
			Screening^a^	T0^b^	T1^c^	T2^d^	FG^e^
**Personal characteristics**							
	Demographics	Standard items	✓	✓			
	Cancer-related characteristics^f^	Standard items	✓	✓			
	Fatigue onset^f^	Developed item	✓				
	Fatigue duration^f^	Developed item	✓				
	Current CCRF^g^ care use^f^	Developed item	✓				
**Primary and secondary outcomes**							
	Intervention completion	Developed items, self-report and therapist log			✓		
	Intervention satisfaction	Developed items based on [39,40]			✓		
	Intervention experiences	Not applicable					✓
	Partner involvement	Developed item, self-report and therapist log			✓		
	Fatigue severity^h^	CIS-fatigue^i^	✓	✓	✓	✓	
**Potential** **mediators: mindfulness- and cognitive-behavioral variables**							
	Self-efficacy	SES^j^ or SES partner version		✓	✓		
	Catastrophizing	J-FCS^k^ or J-FCS partner version		✓	✓		
	Mindfulness	FMI^l^		✓	✓		
**Other relevant measures**							
	Emotional well-being	HADS^m^		✓	✓	✓	
	Relationship satisfaction	MMQ-marital satisfaction^n^		✓	✓	✓	
	Caregiver burden regarding patient fatigue^o^	ICQ^p^, partner version		✓	✓		
	Perceived change in fatigue^f^	Developed item based on [41]			✓		
	Adverse events	Developed items based on [41], self-report and therapist or recruitment log			✓		
	Supportive care use for mental health issues	Developed items based on [41]		✓			

^a^Some screening items will be assessed verbally on the phone (eg, relationship status), others through a questionnaire (eg, fatigue items).

^b^T0 is baseline.

^c^T1 is 2 weeks after completion of the intervention.

^d^T2 is 1 month after T1.

^e^FG: focus group.

^f^Patient only.

^g^CCRF: chronic cancer-related fatigue.

^h^For partners at baseline and T1 only.

^i^CIS-fatigue: Checklist Individual Strength, subscale Fatigue Severity [42,43].

^j^SES: Self-Efficacy Scale [44].

^k^J-FCS: Jacobsen Fatigue Catastrophizing Scale [45].

^l^FMI: Freiburg Mindfulness Inventory Short Form [46].

^m^HADS: Hospital Anxiety and Depression Scale [47,48].

^n^MMQ: Maudsley Marital Questionnaire, subscale Marital Satisfaction [49,50].

^o^Partner only.

^p^ICQ: Illness Cognition Questionnaire [51].

Demographic characteristics will be assessed at the screening and T0 and include self-reported age, sex, level of education, occupational status, relationship status and duration, cohabitation status and duration, and comorbidities.

Patients’ cancer-related variables are self-reported and include cancer type, prognosis, presence of metastasis, treatment received, time since diagnosis, and time since treatment completion.

Intervention adherence will be assessed at T1, as self-reported by the patients and as registered by the therapists in their therapy log. The item used reads: “Did you/your client complete all sessions of the COMPANION therapy?” Answer categories are (1) “Yes, I/my client completed all sessions of the intervention” and (2) “No, I/my client stopped after session ____ (fill in the blank).” Reasons for stopping can be recorded in a free text field. By design, partners’ involvement in the intervention is flexible, as this was an important requirement derived from the preceding needs assessment study ([name] et al, unpublished data, 2023). We consider receiving 6 sessions to be the minimal therapeutic dose. Therefore, intervention completion is achieved when a patient receives ≥6 out of 9 sessions, as reported by the patient at T1 and/or in the postintervention therapist log, and the partner did not drop out from the intervention.

Intervention satisfaction will be assessed with items based on those of other pilot trials for patients and their loved ones [39,40]. For both patients and partners, a total of 2 items will be used to assess satisfaction with the intervention overall (ie, “Overall, how satisfied are you with the COMPANION therapy?”) and satisfaction with the couple approach (ie, “How satisfied are you with the possibility of jointly participating in the COMPANION therapy?”). Additional items assess satisfaction with specific aspects of the intervention. Items are scored on a 7-point Likert scale; scores 5 to 7 represent (high) satisfaction.

Fatigue severity will be assessed using the CIS-fatigue. A total of 8 items assess fatigue severity during the past 2 weeks (eg, “I feel tired”) and are scored on a 7-point Likert scale, ranging from (score 1) “Yes, that is true” to (score 7) “No, that is not true.” A higher sum score indicates more severe fatigue (range 8-56), with a score of ≥35 indicating severe fatigue in patients with cancer [42,43]. A clinically relevant change is operationalized as a difference of 6 points [52].

Recruitment rates: the research assistant will complete a recruitment log. The following information will be collected: (1) number of patients approached for recruitment (through the UMCG and HDI); (2) number of participants (ie, patient and/or their partner) interested in participation; (3) number of included couples; and (4) number of couples dropping out from the intervention and study. Along with these rates, reasons will be recorded. The recruitment rate is defined as the average number of couples included per month.

Adherence to the study protocol will be recorded by the research assistant in the recruitment log in terms of the number and percentage of questionnaires completed. Completion is defined as having responded at least to the items assessing the outcome measures.

Potential mechanism variables will be assessed in the weekly diary and include affect, sleep, catastrophizing, partner communication, partner interactions, self-efficacy, mindfulness, and closeness. Items are based on and adapted from a daily diary study among survivors of cancer and their partners [20,21,53] and existing scales. Table 3 provides an overview of the items.

**Table 3 table3:** Concepts assessed with the diary method. Participants complete weekly diaries starting the week before the intervention, during the course of the intervention, and the week following the end of the intervention (ie, a total of 17-22 weeks) to assess potential working mechanisms of COMPANION.

Constructs		Items and instruments	Time frame

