**Feasibility of trial procedures**					
	Rates related to the recruitment procedure	Recruitment rate: average per month, averaged across recruitment strategies.	Recruitment log	≥3 couples included per month	<1.5 couples included per month
	Adherence to the T1 and T2 questionnaires	Percentage of patients and partners completing and returning T1 and T2.	T1 and T2 (patients and partners), recruitment log	≥65% of patients and partners completed T1 and ≥60% of patients and partners completed T2	<33% of patients and partners completed T1 and <30% of patients and partners completed T2
	Adherence to the diary protocol	Percentage of diaries completed by patients and partners.	Diary (patients and partners), recruitment log	≥65% of diaries completed by patients and partners	<33% of diaries completed by patients and partners

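### Adverse event items are scheduled once, at T1, and not at T2, so the last month of follow-up has no scheduled collection and T1 non-responders leave no self-report

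*Protocol article*

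**What the plan says.** Table 2 (Measures) places adverse events among the other relevant measures. The source is "Developed items based on [41], self-report and therapist or recruitment log", and T1 is the only time point ticked. In the same block, HADS and marital satisfaction are ticked at T0, T1 and T2. Patient CIS-fatigue is also taken at T2.

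The table's caption sets the default respondents: "Unless otherwise indicated, both patients and their partners complete questionnaires, and they report on their own health, perception, and state". The adverse events row carries no mark limiting it to one member of the couple, while the row directly above it is marked for patients only. Both members therefore answer the items at T1.

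The footnotes fix the timing: "T1 is 2 weeks after completion of the intervention" and "T2 is 1 month after T1". The Design section plans 15 to 20 weeks for the intervention. Table 3, which lists the weekly diary content, has no adverse event entry, and the Assessments section ends the diaries one week after the intervention.

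The Assessments section describes the therapist log as a record of delivery and the recruitment log as a record of recruitment and study adherence. Only Table 2 links either log to adverse events. The Table 4 benchmark for the questionnaires is "≥65% of patients and partners completed T1 and ≥60% of patients and partners completed T2". The Explorative Analyses section uses T2 for patient fatigue and, for both members, HADS and marital satisfaction.

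**The concern.** Effects are explored to T2, but the adverse event items stop at T1. By then the sessions have ended, the diaries have ended, and with them the calls prompted by missed diaries. Nothing in the schedule asks anyone about an adverse event in the month that follows, although a questionnaire is sent to both members at the end of it.

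The single self-report also reaches only those who answer T1. People who stop the intervention may be less likely to answer, and some may have stopped because it went badly for them. That is a plausible inference, not something the article states.

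At stake is how complete the safety summary is. The pilot is meant to inform whether a randomized trial should follow, and the Discussion presents it as the first test of a couple mindfulness intervention aimed mainly at this kind of fatigue. A count drawn largely from T1 responders would probably be too low, and a reader could not tell by how much unless the number without self-report is given.

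**Working it through.** **The plan's own figures.**
- Sample size: the article requires 27 patients and assumes 20% drop-out. 27 / 0.80 = 33.75, rounded up to 34 couples, as stated. That is 34 × 2 = 68 people.
- Diary span: one week before, 15 to 20 weeks of intervention, one week after. 1 + 15 + 1 = 17 and 1 + 20 + 1 = 22, which matches Table 3's caption ("a total of 17-22 weeks").

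**Share of follow-up with no scheduled adverse event collection.** Inputs: 15 to 20 weeks (Design), 2 weeks to T1 (Table 2 footnote), and about 4 weeks from T1 to T2 (the footnote says 1 month; the Secondary Aims and Discussion say 4 weeks).
- Start to T1: 15 + 2 = 17 weeks, up to 20 + 2 = 22 weeks.
- Start to T2: 17 + 4 = 21 weeks, up to 22 + 4 = 26 weeks.
- Share after T1: 4 / 21 = 19.0%, down to 4 / 26 = 15.4%.

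**People with no self-report.** Expected number = 68 × (1 − T1 response).

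| T1 response | Where it comes from | Calculation | No self-report |
|---|---|---|---|
| 80% | Drop-out assumed in the sample size section | 68 × 0.20 = 13.6 | about 14 |
| 73% | Completion in the previous trial (Secondary Aims) | 68 × 0.27 = 18.36 | about 18 |
| 65% | Table 4 benchmark | 68 × 0.35 = 23.8 | about 24 |

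The first row assumes that both members of a couple that drops out miss T1. The second applies a rate seen in patients to partners as well. The third is a deliberately conservative benchmark, so it is better read as the upper end of what the plan would accept than as a forecast.

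**The case against.** The strongest reply is that safety information does not rest on one question. Therapists read patients' logs and give feedback weekly. There are three video calls with patient, partner and therapist together. For either member, "if 2 consecutive diaries have not been responded to, the assistant will call the participant to discuss possible problems". The recruitment log records couples who drop out of the intervention or the study, with reasons, and the adherence item has free text for reasons for stopping. The study is classed as negligible risk. Definitions, recall period and log procedures normally belong in a full protocol, which is not at hand.

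Most of this stands, and it rules out several stronger readings that a reader might infer:

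- *Partners depend on the logs alone.* They do not; they self-report at T1. Their other contact is thinner ("Partners will have access to these materials through the patient", and their involvement is flexible), but only partners who miss T1 rely on the logs.
- *Harm is measured once while benefit is measured throughout.* HADS and marital satisfaction for both members, and patient CIS-fatigue, can show worsening at T2, and weekly affect can do so during the intervention. Only the adverse event items stop at T1.
- *Nothing can be recorded between T1 and T2.* The recruitment log also serves T2 adherence and study drop-out, so a spontaneous report might be entered. What is missing is scheduled collection.
- *Recall covers 17 to 22 weeks.* The article states no look-back period for these items. The interval from start to T1 equals the diary span only by coincidence of arithmetic.
- *A given fraction of events will be missed.* That would need event rates in responders and non-responders and the yield of the logs, none of which the article gives.

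The reply does not remove the central point. Table 2 presents itself as an overview of the constructs and their time points, and it leaves T2 blank for adverse events while ticking T2 for other scales in the same block. That is a stated schedule, not a detail lost in shortening the protocol.

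**Conclusion.** The point holds in a narrow form and is minor. Adverse event items are scheduled for both members at T1 and not at T2, so the final 15% to 19% of the time from start of intervention to T2 has no scheduled collection. Between about 14 and 24 of 68 people would have no self-report and would rely on the therapist or recruitment log.

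These figures assume full recruitment of 34 couples, an intervention within the planned 15 to 20 weeks, a four-week interval from T1 to T2, and T1 response between 80% and 65%. The article supports no estimate of how many events would go unrecorded. No sample size, endpoint or benchmark is affected.

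**What to change.** 1. In Table 2, tick adverse events at T2 for patients and partners, using the existing items. Ask those who answered T1 about the period since T1, and those who missed T1 about the period since the start of the intervention.
2. Report adverse events over all included patients and partners, separately by source (self-report, therapist log, recruitment log), and state how many people gave no self-report.

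The cost is a few more items in a questionnaire already being sent, and possibly a higher adverse event count. The first step closes the T1 to T2 gap for those who answer T2. It recovers T1 non-responders only in part, since some will miss T2 as well (its benchmark is 60%), which is why the second step is needed. An adverse event item in the weekly diary is not proposed: it would add to a burden the article already acknowledges, and the diaries end before T1.

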**Outcome variables**			
	Fatigue severity^a^	1 item, as in [20,21,53]	Momentary^b^
	Fatigue severity^c^	4 items based on SFQ^d^	Last week^e^
	Intervention adherence	1 developed item	Last week
	Partner involvement	2 developed items	Last week
